## Abstract

**Background:** Despite the rapid advance of neonatal care, bronchopulmonary dysplasia (BPD) remains a significant burden for the preterm population, and there is a lack of effective intervention. Stem cell depletion because of preterm birth is regarded as one of the underlying pathological mechanisms for the arrest of alveolar and vascular development. Preclinical and small-sample clinical studies have proven the efficacy and safety of stem cells in treating and preventing lung injury. However, there are currently no randomized clinical trials (RCTs) investigating the use of autologous cord blood mononuclear cells (ACBMNC) for the prevention of BPD in premature infants. The purpose of this study is to investigate the effects of infusion of ACBMNC for the prevention of BPD in preterm neonates <28 weeks.

**Methods:** In this prospective, randomized controlled double-blind multi-center clinical trial, 200 preterm neonates <28 weeks gestation will be randomly assigned to receive intravenous ACBMNC infusion (5 × 10^7^ cells/kg) or placebo (normal saline) within 24 h after birth in a 1:1 ratio using a central randomization system. The primary outcome will be survival without BPD at 36 weeks of postmenstrual age or at discharge, whichever comes first. The secondary outcomes will include the mortality rate, other common preterm complication rates, respiratory support duration, length, and cost of hospitalization, and long-term outcomes after a 2-year follow-up.

**Conclusion:** This will be the first randomized, controlled, blinded trial to evaluate the efficacy of ACBMNC infusion as a prevention therapy for BPD. The results of this trial will provide valuable clinical evidence for recommendations on the management of BPD in extremely preterm infants.

**Clinical Trial Registration:** ClinicalTrials.gov, NCT04440670, registered 06/18/2020, prospectively registered, https://clinicaltrials.gov/study/NCT04440670?term=NCT04440670&rank=1 (Additional File 2).

## Background

Preterm birth, a significant growing health concern around the world, affects 5–18% of newborn infants (1, 2). Bronchopulmonary dysplasia (BPD) is a severe and frustrating preterm complication causing adverse long-term outcomes (3, 4). The incidence of BPD in extremely preterm neonates was reported to be as high as 68% (5). The disruption of normal pulmonary vascular and alveolar growth after early birth subjects these infants to increased cardiopulmonary morbidity and mortality (6, 7). Currently, with the improvement of intensive care interventions, the mortality rate of extremely preterm neonates with BPD has decreased (7–9). However, many survivors still face a lifetime of disability, including long time dependence of oxygen therapy, asthma, and repeated hospital admission because of pneumonia even in developed countries (4, 6). Although new ventilation strategies and pharmacological treatments have been applied, there are no curative therapies available to target the underlying structural changes of the lungs leading to the symptoms (3).

The cord blood mononuclear cell (ACBMNC) layer is rich in valuable stem and progenitor cells (SPC) (10, 11). Although it is capable of self-renewal, it also has the potential to differentiate into various cellular phenotypes. In addition, its paracrine effect contributes to tissue repair and immune modulation (7, 11, 12). Animal studies have demonstrated the beneficial effects of the infusion of cord blood stem cells in the prevention and treatment of lung injury, including experimental BPD (13–15). Evidence from several clinical trials has proven the safety and feasibility of autologous cord blood infusion in neonates (9, 16–20). However, there is very limited data regarding its effects on preventing BPD, especially among extremely low-birth weight (ELBW) infants.

With these concepts in mind, the authors have tried to clarify the effects of ACBMNC cell infusion for the prevention of BPD since 2009. In the first study performed at our hospital, the safety and feasibility of ACBMNC infusion in preterm infants was demonstrated (9). Subsequently, we compared the effectiveness of ACBMNC infusion in those patients at our center (8). We found that ACBMNC infusion resulted in a significant decrease in the duration of mechanical ventilation (3.2 vs. 6.41 days, *p* = 0.028) and in the need for oxygen therapy (5.33 vs. 11.31 days, *p* = 0.047) (8). Given the small sample size and comparatively high gestational age of the enrolled preterm infants, no statistically significant differences in BPD incidence were observed in the previous small-sample trial. Therefore, our aim is to conduct a large-scale, multi-center, blinded randomized clinical trial (RCT) to evaluate the efficacy of ACBMNC infusion in BPD prevention in extremely preterm neonates.

## Methods and Analysis

### Study Design and Settings

This study protocol describes a randomized, placebo-controlled, double-blinded, multi-center trial to be conducted at 14 medical centers (Table 1) in tertiary hospitals. The participating Neonatal Intensive Care Units (NICU) were selected by the expert committee based on the distance to Guang Dong Cord Blood and Stem Cell Bank and the level of intensive care that the NICUs could provide. The Guang Dong Cord Blood and Stem Cell Bank is a public provincial blood bank affiliated with the Guangdong Women and Children Hospital and collects cord blood routinely at these hospitals. To ensure that the cord blood would be processed and infused to the infants within 24 h after birth, the distance of these centers should fulfill this criterion. Furthermore, the NICUs in the selected centers are members of Guangdong Neonate Intensive Care Network. The staff working at these centers has been trained by the NICU of the Guangdong Women and Children Hospital, which means the selected centers use similar guidelines regarding treatment of patients. All the centers will hold quality control meetings frequently to ensure research consistency. A total of 200 neonates fulfilling the eligibility criteria will be enrolled. Subsequently, the participants will be randomly divided into two groups [ACBMNC infusion group and control [placebo] group] at a 1:1 ratio. The protocol for this study has been developed based on Standard Protocol Items: Recommendations for Interventional Trials (SPIRIT) checklist (Additional File 1). We have followed the Consolidated Standards of Reporting Trials (CONSORT) guidelines and the study design is illustrated in Figure 1. Consort flow diagram.

**Table 1 T1:** Research centers.

01	Department of neonatology, Guangdong Women and Children Hospital
02	Department of neonatology, Sun Yat-sen Memorial Hospital, Sun Yat-sen University
03	Department of neonatology, The third Affiliated Hospital of Sun Yat-sen University
04	Department of neonatology, Nanfang Hospital, Southern Medical University
05	Department of neonatology, Zhongshan Boai Hospital
06	Department of neonatology, Foshan Chancheng Central Hospital
07	Department of neonatology, Foshan Women and Children Hospital
08	Department of neonatology, Guangdong Second Provincial General Hospital
09	Department of neonatology, Hexian Memorial Affiliated Hospital of Southern Medical University

**Figure 1 F1:**
[figure not shown]
Flow diagram.

### Trial Objectives

#### Primary Objective

The primary objective of this trial is to evaluate the efficacy of ACBMNC infusion in preventing BPD at 36 weeks of postmenstrual age or at discharge, whichever comes first, in extremely preterm infants (20).

#### Secondary Objectives

The secondary objectives of this trial are (1) to compare the infant mortality rate at 36 weeks of postmenstrual age; (2) to compare the rate of other common preterm complications included intraventricular hemorrhage (IVH), necrotizing enterocolitis (NEC), retinopathy of prematurity (ROP), respiratory distress syndrome (RDS), ventilation-associated pneumonia (VAP), hypoxic ischemic encephalopathy (HIE), late-onset sepsis (LOS), and anemia; (3) to compare the duration of mechanical ventilation and oxygen therapy in the two groups; (4) to determine re-intubation rate and time return to birth weight (BW); (5) to compare the duration of antibiotic usage; and (6) to determine the long-term outcomes after a 2-year follow up, including anthropometric characteristics, respiratory outcomes, and neurodevelopmental outcomes via standardized neurological examination.

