#### Randomization

The randomization sequence will be generated electronically using SPSS (version 21). Following enrolment, treatment will be assigned after verification of eligibility and consent status. Computer generated randomization will be performed by the statistician in our center at a 1:1 ratio. A randomization number will be assigned by computer for each enrolled infant. Infants will be randomized to the order in which they receive ACBMNC and placebo infusions. Those enrolled in the ACBMNC group will receive an infusion of ACBMNC within 24 h after birth. Those in the placebo group will receive an infusion of a placebo solution, consisting of normal saline with the same volume. Cell dose for all patients to be targeted at 5 × 10^7^ cells per kilogram.

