
#### Trial Treatment Methods

Eligible infants will be observed at the NICU of the Guangdong Women and Children Hospital until discharge home. All patients in the study will be given intensive care therapy in accordance with departmental guidelines, which include therapies such as positive pressure mechanical ventilation, non-invasive respiratory support, oxygen therapy, and exogenous surfactant replacement (Curosurf, Chiesi, Parma, Italy). Chest radiographs will be performed at admission and 8 h after CBT on the first day of life in all surviving patients. Blood gas will be monitored every 24 h until weaning from ventilation. All clinical diagnoses will be defined according to a standard reference (16). Soon after the preterm infant is delivered, written consent will be obtained from the parents, and ACBMNC infusion was applied to the baby in addition to routine pulmonary surfactant replacement, and mechanical ventilation support as indicated. Those assigned to the ACBMNC group will receive an infusion of ACBMNC with 24 h after birth. Infants in the control group will receive an infusion of a placebo solution consisting of normal saline with the same volume. Cell dose for all patients will be targeted at 5 × 10^7^ cells per kilogram.

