#### Basic Clinical Data Collection

The following data will be collected: (1) clinical basic characteristics including sex, gestational age, birth weight, delivery mode, Apgar score at 1, 5, 10 min; (2) characteristics of cord blood processing including cord blood volume, cell number, cell concentration before and after processing, CFU-GM, CD34+ cell count, cell viability post processing; (3) characteristics of infusion cells including total cell number, time between collection (birth) and initiation of infusion, infused volume, and pathogen detection (including bacteria culture, fungus culture, HIV, HBV, HCV, CMW, and *Treponema pallidum*) results; and (4) other routine clinical interventions including dose and times of pulmonary surfactant (PS) replacement, postnatal steroid use, surgical closure of patent ductus arteriosus, and use of blood products.

We will use the following clinical definitions in this study:

Gestational age will be determined on the basis of a combination of the last menstrual period and early ultrasound findingsThe diagnosis of common preterm complications will include the following (23):

BPD, defined as treatment with oxygen >21% for at least 28 days, and its severity will be assessed at 36 weeks of postmenstrual age or discharge home whichever comes first. Mild BPD, defined as breathing room air at assessment. Moderate BPD, defined as the need for <30% supplemental oxygen, and severe BPD defined as needing ≥30% supplemental oxygen or positive airway pressure. For these patients, BPD status will be analyzed by a committee of three independent experts blinded to the study group.

RDS will be defined if the infants show evidence of respiratory symptoms such as grunting and chest retraction, typical chest radiograph findings, and/or treatment with surfactant, and the need for assisted ventilation.

NEC will be defined using Bell's classification. Infants with stage II or above will be diagnosed with NEC.

LOS will be defined if the infants had a positive bacterial culture results after the first 72 h after birth.

ROP will be defined according to the International Classification for Retinopathy of Prematurity.

Anemia will be defined as hemoglobin no more than 140 g/L.

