### Outcome Measures

*Primary outcome measure:*

- The frequency of BPD or death in at 36 weeks of postmenstrual age or discharge home whichever comes first.

*Secondary outcome measures:*

- Mortality rate- Incidence of BPD- Incidence of other preterm complications including IVH, PVL, NEC, ROP, RDS, VAP, LOS, and anemia [all clinical diagnoses will be defined according to a standard references (16)].- Duration of hospitalization.- Duration of mechanical ventilation and oxygen therapy- Frequency of re-intubation.- The time (days) return to BW.

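### RDS is compared between arms as a secondary outcome, but its definition can be met before the infusion, so any treatment effect on it is diluted

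*Protocol article*

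**What the plan says.** Secondary objective (2) in the protocol article compares complication rates between the groups, including "respiratory distress syndrome (RDS), ventilation-associated pneumonia (VAP), hypoxic ischemic encephalopathy (HIE"). The Outcome Measures section lists "Incidence of other preterm complications including IVH, PVL, NEC, ROP, RDS, VAP, LOS, and anemia". RDS is in both lists; HIE is only in the first.

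Under Basic Clinical Data Collection, "RDS will be defined if the infants show evidence of respiratory symptoms such as grunting and chest retraction", together with "typical chest radiograph findings, and/or treatment with surfactant, and the need for assisted ventilation". No time of onset is attached. Other complications in the same set of definitions do carry a time condition: a positive culture counts as LOS only after the first 72 h, and VAP requires more than 48 h of ventilation. HIE is not defined.

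On timing, the Randomization section says that infants in the cell arm "will receive an infusion of ACBMNC within 24 h after birth". Trial Treatment Methods describes the cells as given "in addition to routine pulmonary surfactant replacement, and mechanical ventilation support as indicated". The cord blood processing section has each unit sent to the bank, tested, separated, counted and returned to the hospital before infusion.

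**The concern.** An infant who has respiratory symptoms, has been given surfactant and is being ventilated can satisfy the RDS definition before any cells or saline are infused. That infant still counts as an outcome event in a comparison of ACBMNC with placebo. To the extent that RDS precedes infusion, the comparison describes how the arms happened to differ before treatment and says little about what the treatment did.

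Two misreadings are at stake. A real effect on later respiratory course could be reported as absent, because it is swamped by cases that it could not have changed. Or a chance difference in early RDS could be reported as benefit or harm of a cell therapy.

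**Working it through.** **Can the definition be met before infusion?** The relevant parts of the protocol, side by side:

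- Ventilation: Table 2 records it at V1 (birth), before the intervention visit V2.
- Radiograph: Trial Treatment Methods schedules one at admission and another 8 h after the infusion.
- Surfactant: Trial Treatment Methods treats it as routine care to which the infusion is added.
- Delay to infusion: the processing section requires transport to the bank, viral PCR and bacterial smear, a 30 min incubation, a 30 min centrifugation, counts and return transport. Study Design and Settings selects centres by distance so that all this fits within 24 h.
- Ascertainment: Table 2 schedules other preterm complications only at V3 (36 weeks), with nothing to separate cases before infusion from cases after it.

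So the definition can be met first, and the design builds in time for that to happen. The protocol does not say in what share of cases it does.

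**The plan's own figure.** No sample size or effect is stated for RDS. The only planned effect is for BPD, 60% against 35%. The stated 59 per group reproduces from the protocol's formula at two-sided 5% and 80% power: (0.60 × 0.40 + 0.35 × 0.65) × ((1.960 + 0.842)/0.25)² = 58.7, rounded up to 59. I borrow the implied risk ratio, 35/60 = 0.583, purely as an illustration. Nothing in the protocol links it to RDS.

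**Dilution.** Let f be the share of RDS cases present before infusion (assumed). These cannot change; the rest are multiplied by 0.583.

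Observed risk ratio = f + (1 − f) × 0.583

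- f = 0.7: 0.7 + 0.3 × 0.583 = 0.875
- f = 0.9: 0.9 + 0.1 × 0.583 = 0.958
- f = 1.0: 1.00

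**Power.** Inputs: 100 per arm (the 200 in Study Design and Settings), two-sided 5%, and an assumed RDS rate of 80% on placebo. Power is for a significant result in favour of ACBMNC.

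| f (assumed) | Visible difference | Power |
|---|---|---|
| 0 | 33.3 points | >99% |
| 0.5 | 16.7 points | 75% |
| 0.8 | 6.7 points | 20% |
| 0.9 | 3.3 points | 8% |
| 1.0 | 0 | no effect to detect |

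At f = 0.9, power ranges from 5.5% to 19% over assumed RDS rates of 60% to 95%. Even if the infusion prevented every later case (0.80 × 0.10 = 8 points), power at f = 0.9 and an 80% rate would be 26%.

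**What a significant result would mean.** At f = 0.9 the pooled rate is (0.800 + 0.767)/2 = 0.783. The smallest significant difference is about 1.96 × √(2 × 0.783 × 0.217/100) = 0.114, or 11.4 points. The true difference is 3.3 points, so at least 11.4 − 3.3 = 8.1 points, about 71%, would be chance. At f = 0.8 the pooled rate is 0.767 and the threshold is 11.7 points; the chance part is then at least 11.7 − 6.7 = 5.0 points, about 43%. The word mostly therefore depends on a high pre-infusion share.

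**The case against.** The strongest reply has four parts.

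*The share of pre-infusion cases is unknown.* This stands. The second radiograph comes 8 h after infusion, and the definition asks for typical radiograph findings without saying which film, so RDS can also be diagnosed after treatment. A reader might infer that the comparison cannot show any effect. That holds only if every case precedes infusion, which the protocol does not say.

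*The comparison is unbiased.* This also stands. Table 2 assigns the random number at V1, so RDS arising between randomisation and infusion is a post-randomisation event, and an all-randomised comparison of it is valid but diluted. For that reason pre-infusion characteristic is a more accurate label than baseline.

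*RDS information is not lost.* Largely correct. Surfactant doses and times are collected, ventilation and blood gas are recorded at V1, and a radiograph is taken at admission. The Statistical Analysis section also allows adjustment for characteristics that differ between groups. A reader might infer that RDS is no longer available to describe the infants before treatment; the protocol does not support that.

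*These are items in a list of secondary complications.* True, and it limits the importance. It does not answer the point, because the protocol names RDS as an outcome and fixes a definition that admits cases complete before treatment. This is not a detail left to an analysis plan.

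A reader might also extend the timing argument to HIE. The protocol says nothing on when HIE arises, so the extension would rest on outside clinical knowledge. What the text does show for HIE is a mismatch between the two lists and no definition.

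**Conclusion.** The point holds for RDS as a matter of dilution and interpretation. The protocol's text establishes that cases complete before infusion count as outcome events. The size rests on three assumptions outside the protocol: the pre-infusion share, the RDS rate, and the use of the BPD risk ratio for later RDS cases. At a 90% share the visible risk ratio is about 0.96, and power with 100 per arm is about 8%; at 50% the loss is much smaller (power 75% against more than 99%). For HIE the finding is only that the objectives and the outcome list disagree and that no definition is given. The primary outcome and its analysis are unaffected, so this is a minor but worthwhile correction.

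**What to change.** 1. Remove all-cases RDS from the complications compared in Secondary Objectives and Outcome Measures. Report RDS present before the start of infusion by arm, as a pre-infusion characteristic. This costs wording, a move between tables, and a yes/no entry at the infusion visit if it cannot be derived from the surfactant, ventilation and radiograph data already collected.

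2. If RDS is to remain an outcome, count only onset after the start of infusion, real or placebo, and state how onset is dated. This costs slightly more. The protocol lists no RDS onset time, and it lists time from birth to infusion under the characteristics of the infused cells, without saying that it is recorded for placebo infants. Both times would be needed in both arms.

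3. Reconcile HIE: either delete it from the objectives, or add it to Outcome Measures with a definition and a stated onset rule. This is wording only.

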### Participants

#### Inclusion Criteria

Infants fulfilling all the following inclusion criteria will be enrolled in this trial: (1) birth at a study hospital; (2) a singleton birth; (3) <28 weeks gestational age, (4) signed informed consent from parents before labor; and (5) available umbilical cord blood (UCB).

#### Exclusion Criteria

Infants will be excluded from the study if: (1) they exhibit severe congenital abnormalities (detected via prenatal ultrasound); (2) mothers present with clinical chorioamnionitis, and (3) mothers are positive for hepatitis B (HBsAg and/or HBeAg) or hepatitis C virus (anti-HCV), syphilis, human immunodeficiency virus (HIV) (anti-HIV-1 and−2), or IgM against cytomegalovirus (CMV), rubella, toxoplasma, and herpes simplex virus.

#### Ethical Approval

This study was approved by the ethics committee of the Guangdong Women and Children Hospital, Guangzhou Medical University.

#### Sample Size

Based on our previous study and others' study (9–16, 21), we found the ACBMNC infusion was effective in reducing respiratory support duration in preterm infants. The rate of BPD among extremely preterm infants in our NICU was 60% (pA). What we expect to be an intended (or at least acceptable) effect of the ACBMNC infusion is 25% reduction in frequency of BPD (pB:35%). To detect this difference with a sensitivity of 80% (α) and an error probability of 5% (β), at least 59 patients per randomization group will be required using the following formula:

$$\begin{array}{l} \text{n}=\left(\text{pA}\left(1-\text{pA}\right)/\text{κ}+\text{pB}\left(1-\text{pB}\right)\right)\left((\text{z}1-\alpha /2+\text{z}1-\beta )/(\text{pA}-\text{pB}\right){)}^{2} \end{array}$$

To account for the possibility of as high as 20% loss to follow-up, our estimated sample size is 140 cases totally.

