### Statistical Analysis

Statistical analyses between the two groups will be performed using an unpaired two-tailed Student's *t*-test or Chi-squared Test as appropriate. A logistic regression model will be used for the entire study population (i.e., without removing deaths) to adjust for the effect of treatment on primary outcome according to baseline characteristics and events known to affect the occurrence of BPD (i.e., gestational age, birth weight and other characters that are different in two groups after initial analysis), and to investigate the effect of treatment on the following outcomes: extubation rates, severe adverse events, and death before discharge. The Breslow-Day test and Corchran-Mental-Haenszel (CMH) test will be used to adjust the data derived from different participating centers. The results will be reported as odds ratio (OR) with 95% confidence intervals (CI). All statistical tests will be two-tailed and a *p* < 0.05 will be considered statistically significant. All statistical analysis will be performed using SPSS 21.0 (IBM).

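### The 59 per group and 80% power are computed for BPD alone, a secondary outcome, while the primary outcome is BPD or death, so the stated power is not that of the primary test

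*Protocol article*

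**What the plan says.** All references are to the protocol article.

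- **Primary outcome.** Outcome Measures gives "The frequency of BPD or death in at 36 weeks of postmenstrual age or discharge home whichever comes first". The Abstract states the complement of the same composite: "The primary outcome will be survival without BPD at 36 weeks of postmenstrual age or at discharge, whichever comes first".
- **Secondary outcomes.** The list in Outcome Measures opens with "Mortality rate- Incidence of BPD- Incidence of other preterm complications", so death and BPD each appear separately as secondary.
- **Primary Objective.** It names BPD only: to "evaluate the efficacy of ACBMNC infusion in preventing BPD at 36 weeks of postmenstrual age or at discharge".
- **Sample Size.** The control rate is introduced by "The rate of BPD among extremely preterm infants in our NICU was 60% (pA" and the target effect is a "25% reduction in frequency of BPD (pB:35", that is, 60% against 35%. The result is 59 per group, raised to 140 in total for up to 20% loss to follow-up.
- **Planned enrolment elsewhere.** The Abstract and Study Design and Settings both give 200.
- **Analysis.** Statistical Analysis fits the logistic model for the primary outcome to the whole study population, with deaths retained.

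**The concern.** The planning rates and the primary outcome refer to different events. Sample Size gives no composite rate, no mortality rate and no assumed effect of treatment on death. It does not say whether the 60% is a share of all admitted infants or only of those who lived long enough to be assessed.

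The 60% cannot easily be read as a composite rate already. Basic Clinical Data Collection defines BPD by at least 28 days of oxygen, so an infant who dies before day 28 cannot meet the definition. Such deaths were either left out of the 60% or counted as non-events. In both cases the rate of BPD or death is a different number.

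What is at stake is the justification for the size of the trial. The only power statement in the article belongs to an outcome that it ranks as secondary. A reader of the eventual primary result, particularly a null one, would have no valid statement of what the trial could detect.

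**Working it through.** **Inputs from the article.** pA = 0.60 and pB = 0.35 (Sample Size); 1:1 allocation, so κ = 1 (Randomization); two-sided 5% level (Statistical Analysis: "All statistical tests will be two-tailed and a" 0.05 threshold). Power is read as 80% and the type I error as 5%. The text attaches the symbols the other way round ("To detect this difference with a sensitivity of 80% (α) and an error probability of 5% (β"), but only this reading gives the stated 59.

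**Step 1: reproduce the stated figure.** The article's formula is

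n = [pA(1−pA)/κ + pB(1−pB)] × [(z₁₋α/₂ + z₁₋β)/(pA−pB)]²

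= (0.2400 + 0.2275) × [(1.960 + 0.842)/0.25]² = 58.7, rounded up to 59.

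The matching power formula is

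power = Φ( |p₁−p₂| / √{[p₁(1−p₁) + p₂(1−p₂)]/n} − 1.960 ).

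At n = 59 it gives Φ(0.25/√(0.4675/59) − 1.960) = 80.2%. The figure is right for BPD incidence.

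**Step 2: move to BPD or death.** The article gives no mortality figure, so control-arm mortality m is assumed to be 10%, 20% or 30%. Three readings are possible.

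- **A.** 60% and 35% are rates among survivors, and mortality is equal in both arms. Composite = m + (1−m)p, so the difference shrinks to 0.25(1−m).
- **B.** 60% and 35% are rates of all infants, and deaths without BPD add equally to both arms. Composite = p + m, so the difference stays at 25 points.
- **C.** As A, but treatment also lowers mortality in the ratio 35/60, so treated-arm mortality is m × 35/60.

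Worked at m = 20%:

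- A: 0.20 + 0.80×0.60 = 0.680; 0.20 + 0.80×0.35 = 0.480. Power at 59 = Φ(0.20/√(0.4672/59) − 1.960) = 61%.
- B: 0.80 against 0.55. Power at 59 = Φ(0.25/√(0.4075/59) − 1.960) = 85%.
- C: treated-arm mortality 0.20 × 35/60 = 0.1167; composite 0.1167 + 0.8833×0.35 = 0.426, against 0.680. Power at 59 = 82%.

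**Step 3: full range, article's formula throughout.**

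| Reading | m | Composite, control v treated | Power at 59/arm | n/arm for 80% |
|---|---|---|---|---|
| A | 10% | 64.0% v 41.5% | 71% | 74 |
| A | 20% | 68.0% v 48.0% | 61% | 92 |
| A | 30% | 72.0% v 54.5% | 52% | 116 |
| B | 10% | 70% v 45% | 81% | 58 |
| B | 20% | 80% v 55% | 85% | 52 |
| B | 30% | 90% v 65% | 93% | 40 |
| C | 10% | 64.0% v 38.8% | 81% | 58 |
| C | 20% | 68.0% v 42.6% | 82% | 57 |
| C | 30% | 72.0% v 46.4% | 83.5% | 54 |

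**Step 4: reading A at the other sizes in the article**, for m = 10%, 20%, 30%:

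- 70 per arm (the 140 in Sample Size, no loss): 78%, 69%, 59%.
- 80 per arm (200 less 20%): 83%, 74%, 65%.
- 100 per arm (the 200 in the Abstract and Study Design and Settings, no loss): 90%, 83%, 74%.

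**The case against.** The strongest reply is that nothing in the article shows a loss of power. Sample Size speaks of extremely preterm infants in the unit and never of survivors, which if anything favours reading B, where power at 59 per arm is at least 80%. Mortality is itself a compared outcome, so some effect on death is conceivable, and under reading C power also stays above 80%. Only reading A loses power. Even there, 100 per arm gives 83% at 20% mortality and drops below 80% only at about 25% (79%) and above. The 80-per-arm figures are probably pessimistic for the primary test: it is reached by 36 weeks or discharge, infants are observed until discharge, and deaths count as events rather than losses.

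All of that stands as a case against asserting a direction. A reader might infer from the mismatch that the trial is underpowered for its primary outcome. The article does not support that inference, because it would need a survivor denominator and unchanged mortality, and neither is stated.

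The reply does not remove the mismatch itself. Under every reading the 80% was calculated for a different event from the one tested. Nor does the figure of 200 settle it, because Sample Size derives 140 and nothing in the article derives 200. The point is also not detail left to a fuller document: the article prints rates, formula and result, and they are for another outcome.

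The Primary Objective naming only BPD is a small matter. Counting death in the endpoint is a usual way of handling it as a competing event, so this is an alignment of wording and not a second fault.

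**Conclusion.** The point holds in this form: the 59 per group and 80% power are correct arithmetic for BPD incidence, a secondary outcome, and are not the power of the primary test of BPD or death.

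The size and sign of the discrepancy cannot be fixed from the article. Over assumed mortality of 10% to 30%, power at 59 per arm runs from 71% down to 52% under reading A, from 81% up to 93% under B, and from 81% to 83.5% under C. These ranges rest on the assumed mortality values, on the article's unpooled formula and on a two-sided 5% level. Calling the trial underpowered would go beyond the evidence; that conclusion is conditional on reading A and on the size actually enrolled.

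**What to change.** Redo the Sample Size calculation on BPD or death. State:

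1. the control-arm composite rate, from the unit's own data if available and otherwise as an explicit assumption;
2. whether the 60% is of all infants or of survivors;
3. the assumed effect of treatment on death as well as on BPD.

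Reconcile the 140 in Sample Size with the 200 in the Abstract and Study Design and Settings. Then report the power, or the detectable difference, at the planned size over a range of mortality. Align the wording of the Primary Objective with the composite at the same time.

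The cost is a recalculation and some redrafting. If the enrolment target is kept, no further infants are needed, but the reported power may be less favourable. Under reading A at 30% mortality, 80% power would need 116 per arm before losses, more than the 100 per arm that 200 provides. In that case the sponsor would have to accept the lower power openly or revisit the size.
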